### Recruitment strategy

Recruitment targets and procedures have been tested in the pilot study^32^ and are based on these data. Recruitment start dates for the collaborating sites will be staggered over a 6-month period.

### Data collection, management and analysis

The trial will use a series of CRFs to record trial activities and RCT site staff will ensure that each CRF is completed properly and stored in the investigator’s site file (ISF). Site staff will make photocopies and post CRFs to the OTTER Trial team using freepost envelopes, according to a standard operating procedure (SOP) so that both sites and the trial centre will have a copy of CRFs.

Participants will complete questionnaires at baseline, 8 weeks and 12 weeks. Participants will be asked to record the frequency for which hand exercises were completed for at least 20 min using a daily diary. Splint wear diaries will be used to capture hours per day of splint wear and will contribute to per protocol analysis of data. Participants will be provided with freepost envelopes in order to return questionnaires and diaries to the trial centre.

Where postal follow-up questionnaires are not received when expected, first they will be chased by post, and if there is no response key endpoint data will be collected over the phone. Up to three phone calls will be made to obtain key endpoint data. If participants wish to withdraw from their randomised intervention, they will still be included in the trial follow-up, unless they request to be excluded from follow-up. Where available, reasons for withdrawal from follow-up will be collected.

The OTTER Research Team will make copies of CRFs, questionnaires and diaries created by or received directly at the trial centre and post them to the relevant site to be filed in the ISF. The original documents will be secured in the Trial Master File.

Eligibility and stratification data will be entered directly onto the OCTRU online randomisation system by site staff. All other data will be entered into the trial database by the OTTER Research Team. The OTTER Trial team will check each CRF for completeness and where appropriate contact the site for missing data. A data management and sharing plan contains fully comprehensive information about all aspects of data management. All data will be processed according to the Data Protection Act 2018. All study-specific documents, except for the signed consent form and letters to participants, will refer to the participant with a unique study participant number/code and not by name.

Quantitative data will be stored on an OpenClinica trial-specific database prepared and managed by OCTRU. Qualitative data will be stored in QRS NVivo and word documents. The database has inbuilt data validation checks and a trial management system for managing data queries. Peer review of data entry will be conducted on 5% of CRFs. Data discrepancies will be reviewed on a regular basis to help clean the data. All data will be securely stored only accessible by authorised personnel agreed by the Principal Investigator, Legal services at the University of Southampton and The OTTER II Trial Steering Committee. Data will be backed up, and participant identifiable data will be stored separately from study data. Trial documentation will be retained for 10 years after completion of study-related activities and managed in accordance with the University of Southampton and the University of Oxford research data management policies.

Audio-recordings from the interviews will be transcribed verbatim, and participants allocated an ID number. The text of the interviewer notes from the telephone interviews will be anonymised and linked to the interview through the ID number. Names of participants, the names of any people discussed, healthcare employees and hospitals will be removed from transcripts and replaced with pseudonymns. Participants will be sent a letter to thank them for taking part in the telephone interview. A ‘future use of interview’ question is included on the consent form which gives copyright to the Universities of Southampton and Oxford to use the material in research, teaching, publications and broadcasting.

### Statistical analysis

The statistical analysis will be carried out by the OTTER II Trial OCTRU trial statistician. As is usual practice for the Oxford Cinical Trials Unit the statistician will not be blind to treatment allocation. There are rigourous checks and balances in place to ensure that the trial statistician cannot bias outcome.

This three-arm trial will first assess the global comparison of differences between the three treatment arms at the 5% level. The primary (global) null hypothesis is that there is no difference between the three arms. Only if this null hypothesis is rejected at the 5% (two-sided) significance level, will the pairwise comparisons be carried out in order to explore where the difference lies:

Verum splint +self-management programme (Group B) versus self-management programme alone (Group A)Placebo splint +self-management programme (Group C) versus self-management programme alone (Group A)Verum splint +self-management programme (Group B) versus placebo splint +self-management programme (Group C)

It is anticipated that there will be an adjustment for multiple testing at this stage, and Bonferroni or a less conservative method will be used. The main analysis will be intention to treat. A per-protocol analysis of the primary endpoint will be performed as part of the sensitivity analyses. A statistical analysis plan will provide full details of all planned analyses.

The statistical analysis of the primary outcome, AUSCAN hand pain score, will be performed using ANCOVA, adjusting for baseline pain and stratification factors. Continuous secondary outcomes will be analysed using similar methods to the primary outcome. The unadjusted secondary binary variables will be compared using χ^2^ tests with logistic regression being used to adjust for stratification and important prognostic factors in a multi-variable framework.

Baseline characteristics for the three groups will be presented using the appropriate descriptive statistics. Baseline characteristics of participants who completed the trial and those who dropped out will be presented and explored in order to ascertain patterns of loss to follow-up. Subgroups will be examined to look for consistency of any observed treatment effects (using interactions). This analysis will be considered of an exploratory nature potentially providing hypotheses for future studies. The study is not powered to examine these in detail and will not therefore report p values for these.

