Therapeutic splinting for thumb base OA aims to minimise or eliminate motion at the thumb carpometacarpal joint (CMCJ)^13^ in order to prevent joint deterioration and/or deformity, decrease pain and increase overall hand function.^14^ The process of designing thumb splints currently lacks detailed reporting but biomechanical principles have been applied to one design to off-load the dynamic forces occurring during functional hand use on a symptomatic CMCJ.^15^ It is known that stabilisation of the CMCJ to reduce pain levels impacts on hand functionality.^16^ Currently, thumb splints are recommended for patients with thumb base OA.^17^ However, the efficacy of splinting based on this approach has not yet been established and forms the rationale for this trial. Some evidence based on small, non-powered samples^18 19^ show thumb splints can help relieve pain; however, evidence to support their effectiveness is not yet fully supported by robust research.^20^ There is insufficient evidence to suggest that the combination of splinting delivered alongside hand exercises is more effective than hand exercises alone^21–23^ and the evidence to support splinting in alleviating hand pain in the medium term is supported by low-level evidence only.^24^ To date, there has also been no examination of any contextual and non-specific patient–practitioner interaction effects associated with splinting in thumb base OA. If this is substantial, optimising the non-specific effects of treatment could improve treatment effectiveness and overall care of people with OA in a safe and cost-effective way.^25 26^ This randomised controlled trial (RCT) protocol was designed in accordance with the Standard Protocol Items: Recommendations for Interventional Trials checklist,^27^ to evaluate the effectiveness, efficacy and cost-effectiveness of thumb splints for people with thumb base OA.

The primary objective of this trial is to determine the clinical effectiveness and efficacy of thumb splints when added to a self-management programme for people with symptomatic thumb base OA. The trial questions:

Is there a benefit of adding a thumb base splint to a self-management programme for people with thumb base OA?Is there a difference in benefit between adding a verum or a placebo thumb base splint to a self-management programme for people with thumb base OA?What are patients’ views and experiences of the effectiveness, acceptability and adherence to the trial interventions?

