### Sample size

The sample size has been calculated based on undertaking a global analysis of covariance (ANCOVA) for the primary outcome, AUSCAN hand pain^42^ at 8 weeks, adjusting for the baseline pain score and stratification factors (including centre and treated hand dominance) across all three treatment arms using the power and sample size package, PASS 11 (PASS 11. NCSS, LLC. Kaysville, Utah, USA. www.ncss.com). Assuming 80% power, a 5% two-sided significance in order to detect a standardised mean difference of 0.4 (a moderate effect size^43^ based on a difference in the AUSCAN hand pain score of 2 points) and assuming a SD of 5, based on data from the OTTER pilot study,^31^ requires 92 participants per arm. Allowing a 20% loss to follow-up at 8 weeks inflates this to 115 participants per arm, giving a total of 345 participants.

The sample size has taken into account the global comparison of the null hypothesis that there is no difference between the three treatment arms, and pairwise comparisons will only be undertaken if this global comparison is statistically significant. No further adjustment for the sample size has been undertaken to allow for multiple testing.

Clustering is not a consideration in sample size as ‘Centre’ is a stratification factor, and although there may be more than one therapist per centre, this should largely ensure balance across treatment arms within each centre. The Data and Safety Monitoring Committee (DSMC) (online supplementary appendix 8) will review the assumptions underlying this sample size calculation after approximately 50% of the participants have been recruited and followed up for 8 weeks, if still within the recruiting period.

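### As worded, a non-significant global test leaves the splint-versus-no-splint and verum-versus-placebo questions without a pain difference or confidence interval

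*Protocol article*

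**What the plan says.** The Statistical analysis section sets the primary hypothesis: "The primary (global) null hypothesis is that there is no difference between the three arms". It then makes the next step conditional: "Only if this null hypothesis is rejected at the 5% (two-sided) significance level, will the pairwise comparisons be carried out". The three comparisons listed are verum splint versus self-management alone (B–A), placebo splint versus self-management alone (C–A), and verum versus placebo splint (B–C). An adjustment for multiple testing, Bonferroni or something less conservative, is anticipated at that stage.

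The Sample size section states the same condition: "pairwise comparisons will only be undertaken if this global comparison is statistically significant".

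The Introduction lists three trial questions. Two are comparative: "Is there a benefit of adding a thumb base splint to a self-management programme for people with thumb base OA" and "Is there a difference in benefit between adding a verum or a placebo thumb base splint to a self-management programme". The third concerns patients' views and experiences and is answered qualitatively.

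The Economic evaluation and analysis section plans mean differences with 95% confidence intervals for costs and effects, with no condition attached. No section makes similar provision for AUSCAN hand pain.

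**The concern.** A global F-test says whether the three means are compatible with equality. It does not say which arms differ or by how much, so it answers neither comparative question. Requiring it to be significant before claiming a pairwise difference is a sound way to limit false claims. The rule as written goes further and governs whether the comparisons are carried out at all.

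This matters most when the result is not significant. Such a trial may have ruled out a 2-point benefit of the splint, or may have left that benefit quite possible. Only the pairwise difference and its interval separate the two. The article itself says thumb splints are in routine use on limited evidence, so a well-estimated null result would be worth having.

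**Working it through.** **Inputs (Sample size section).** "Assuming 80% power, a 5% two-sided significance in order to detect a standardised mean difference of 0.4"; the raw difference is "based on a difference in the AUSCAN hand pain score of 2 points"; "assuming a SD of 5, based on data from the OTTER pilot study"; 92 evaluable per arm; 20% loss; 115 per arm; 345 in total. Randomisation is 1:1:1. No precision gain from baseline adjustment is assumed below. Differences are signed so that a positive value is a benefit.

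**1. Reproducing the plan's figure.** The non-centrality of the three-arm F-test is λ = n·Σ(μᵢ − μ̄)²/σ², on 2 and 3·92 − 3 = 273 degrees of freedom.
- One arm 2 points from the other two (0, 0, 2): Σ(μᵢ − μ̄)² = 2.667, λ = 92 × 2.667/25 = 9.81, power 80.3%. The smallest n per arm giving 80% power is 92, as stated.
- 92/0.8 = 115, and 3 × 115 = 345, as stated.

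The sample size is therefore right for the global test.

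**2. How often the pairwise step would be skipped (92 per arm).** This is 1 minus the power of the global test; simulation agrees.

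| True means (points) | λ | Global test not significant |
|---|---|---|
| No difference | 0 | 95% |
| One arm differs by 1 | 2.45 | 73% |
| Placebo midway (0, 1, 2) | 7.36 | 33% |
| One arm differs by 2 | 9.81 | 20% |

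**3. Precision of the estimates that would be withheld.** SE = 5 × √(2/92) = 0.737.
- Unadjusted 95% interval: half-width 1.969 × 0.737 = 1.45 points.
- Bonferroni interval for three comparisons (α = 0.05/3): half-width 2.409 × 0.737 = 1.78 points with the t quantile (1.76 with the normal quantile).

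Both are narrower than the 2-point target, so a null trial of this size can be informative.

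**4. What those intervals would have shown (simulation: global F-test, then the B–A interval).**
- No true effect: among trials stopped by the global test, the upper limit of B–A lies below 2 points in 78% (unadjusted) or 62% (Bonferroni).
- Placebo midway, true B–A of 2 points: among stopped trials, the unadjusted interval excludes 2 points in only about 8%. In about 92% the target benefit remains open.

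The same non-significant global result thus covers both situations.

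**5. A side effect of estimating only after significance.** Among trials that pass the global test, the mean B–A estimate is 2.21 for a true 2.0 when only the verum arm differs, 2.38 for a true 2.0 when placebo is midway, and 1.71 for a true 1.0 when only the verum arm differs.

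**The case against.** The conditional sentence sits among hypothesis-testing language: a null hypothesis, a significance level, an adjustment for multiple testing. In that setting, pairwise comparisons may simply mean post-hoc tests. Neither section says that differences or intervals will be withheld, and the planned ANCOVA produces them anyway. The article refers to a statistical analysis plan for full details; that plan is not shown and may provide for estimates in every case. This stands, and it limits how firmly one can predict what would be reported. It does not remove the problem: the condition is stated twice in restrictive terms, nothing in the article separates testing from estimation, and a plan that reported the comparisons regardless would depart from the protocol's wording.

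The testing strategy itself is legitimate. Sample size and analysis agree on a global primary hypothesis, and the 92 per arm reproduces. That also stands; there is no error in sample size or type I error here.

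The size depends on the scenario. The 78% uses unadjusted intervals although an adjustment is anticipated, and the 33% assumes a midway placebo effect that the article does not state. Hence the ranges.

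A reader might infer that a non-significant trial would certainly yield no effect estimates, or would answer none of its questions. The article does not support that. The qualitative question is unaffected, cost and effect differences carry no such condition, and the withholding of pain estimates follows only from a literal reading.

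**Conclusion.** The point holds as a defect of wording in a stated rule. Followed literally, a non-significant global test leaves B–A and B–C without an AUSCAN pain estimate or interval, and nothing else in the article supplies one. With 92 per arm, SD 5 and no gain from covariates, that happens in about 20% of trials when one arm differs by 2 points, 33% when placebo is midway, and 95% when there is no effect. In 62% to 78% of the stopped no-effect trials, the lost B–A interval would have excluded a 2-point benefit. Using the global test to restrict significance claims is acceptable and need not change. Confidence is high that the rule is written this way, and moderate that estimates would be withheld in practice, because the analysis plan is not shown.

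**What to change.** In the Statistical analysis section, and consistently in the Sample size section, state that adjusted mean differences with confidence intervals for B–A, B–C and C–A, from the planned ANCOVA, will be reported whatever the result of the global test and interpreted against the 2-point target difference. Add that the global test restricts only claims of pairwise statistical significance. Say whether the intervals are unadjusted or match the multiplicity adjustment, since the half-width is 1.45 or 1.78 points accordingly. If the analysis plan already says this, the protocol wording should be brought into line with it.

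The cost is two or three sentences. The same model yields the contrasts, the sample size stays at 345, and the type I error of significance claims is unchanged.

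### With three arms the 5% global test already protects the pairwise tests, so the further multiplicity adjustment is unnecessary for them and only costs power

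*Protocol article*

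**What the plan says.** The Statistical analysis section sets the order of testing. "This three-arm trial will first assess the global comparison of differences between the three treatment arms at the 5% level". The gate is explicit: "Only if this null hypothesis is rejected at the 5% (two-sided) significance level, will the pairwise comparisons be carried out". The three comparisons are verum splint versus self-management alone (B versus A), placebo splint versus self-management alone (C versus A) and verum versus placebo splint (B versus C). The section then anticipates an adjustment for multiple testing at the pairwise stage and says that "Bonferroni or a less conservative method will be used". Full analysis details are left to a statistical analysis plan.

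The Sample size section bases 92 participants per arm on the global ANCOVA, repeats that "pairwise comparisons will only be undertaken if this global comparison is statistically significant", and says that the sample size was not adjusted further for multiple testing.

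**The concern.** The plan applies two layers of multiplicity protection to the same three tests: the global gate, then a correction of the pairwise p-values. With four or more arms the second layer can be needed, because a partial null with several true pairwise hypotheses can hold while the global null is false. With three arms no such partial null exists, so the second layer adds nothing to the familywise error control of the tests.

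The cost falls on what the trial most wants to know. Both quantitative trial questions (end of the Introduction) are answered by pairwise comparisons: does adding a splint help, and does verum differ from placebo. The sample size covers the global test only, so any power lost at the pairwise stage has not been budgeted for.

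**Working it through.** **Inputs from the Sample size section.** "Assuming 80% power, a 5% two-sided significance in order to detect a standardised mean difference of 0.4", "based on a difference in the AUSCAN hand pain score of 2 points", "assuming a SD of 5, based on data from the OTTER pilot study"; 92 evaluable per arm; 20% loss to follow-up. The Randomisation section gives 1:1:1 allocation. The mean of the third arm is not stated. I assume a range, written as benefit over A for (A, B, C): (0,2,0), (0,2,2), (0,2,1) and, as a wider case, (0,4,2).

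**Step 1: reproduce the planned size.** The noncentrality of the global F-test is λ = n·Σ(μᵢ − μ̄)²/σ².
- For (0,2,0), or equally (0,2,2), Σ(μᵢ − μ̄)² = 4/9 + 16/9 + 4/9 = 2.667, so λ = 92 × 2.667/25 = 9.81. With 2 and 273 degrees of freedom, power is 80.3%, and 92 is the smallest n that reaches 80%.
- 92/0.8 = 115 per arm, and 3 × 115 = 345. The planned figures are reproduced.
- For (0,2,1), λ = 92 × 2/25 = 7.36 and global power is 67.4%.

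**Step 2: familywise error with the gate and no further adjustment.** There are three cases.
- All three means equal: no pairwise test is reached unless the 5% global test rejects, so the error is at most 5%.
- Exactly one mean differs: only one pairwise null is true, and it is tested at 5%.
- All means differ: no pairwise null is true.

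Any two true pairwise nulls imply the global null, so this is a closed test with strong control at 5%.

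Simulation (400,000 trials per scenario, pooled variance, 273 degrees of freedom) agrees. Familywise error is 0.0496 under the full null and 0.049 to 0.050 under the partial nulls, including very large effects. Adding Bonferroni (0.05/3 = 0.0167 per test) lowers it to 0.042 under the full null and 0.017 under a partial null at the design effect.

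**Step 3: power after the gate, n = 92 per arm, SD 5.**

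| Means (A,B,C) | Comparison | Unadjusted 5% | Bonferroni | Loss (points) |
|---|---|---|---|---|
| (0,2,0) | B–A | 72.2% | 61.8% | 10.4 |
| (0,2,0) | B–C | 72.2% | 61.8% | 10.4 |
| (0,2,0) | B–A and B–C both | 64.2% | 46.2% | 18.0 |
| (0,2,2) | B–A | 72.1% | 61.7% | 10.4 |
| (0,2,1) | B–A | 66.2% | 61.6% | 4.6 |
| (0,2,1) | B–C | 25.8% | 14.8% | 11.0 |
| (0,4,2) | B–C | 77.1% | 62.1% | 15.0 |

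**Step 4: the milder methods, where the largest difference is 2 points.**

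| Method after the gate | Loss per true comparison (points) | Loss for B beating both A and C, (0,2,0) |
|---|---|---|
| Shaffer | about 1–3 | about 2 |
| Hochberg | about 3–7 | about 11 |
| Holm | about 4–7 | about 11.5 |
| Tukey | about 4–10 | about 16 |

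**Step 5: sensitivity.** If baseline pain explains 25% of the variance, or if all 115 per arm are retained, the Bonferroni loss is about 4 to 14 points per comparison and 14 to 16 points for beating both comparators.

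**Scale.** For one two-sample comparison with 80% power, n per arm = 2σ²(z₁₋α/₂ + z₀.₈)²/δ² = 12.5 × (z₁₋α/₂ + 0.842)². This gives 98.1, so 99, at α = 0.05 and 130.9, so 131, at α = 0.0167, against 92 planned.

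**The case against.** The strongest reply is that the protocol does not commit to Bonferroni. It anticipates an adjustment, allows a less conservative method and leaves details to the analysis plan. That stands: the Bonferroni figures are the upper end of what the text permits, not the cost of a fixed decision. It does not remove the point, because some adjustment is stated and each method examined lowers power at the stated 2-point effect without improving the control of the tests.

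An extra adjustment is also conservative rather than invalid, and gated pairwise power for B versus A is only 66% to 72% at the 2-point effect even without it. Both are true. This is a matter of efficiency, and the correction is not the main reason why pairwise power falls below 80%.

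Third, closure protects hypothesis tests only. Unadjusted 95% intervals have no simultaneous coverage, which Bonferroni or Tukey intervals can supply. This also stands and limits the claim to the tests.

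Three stronger readings are tempting but not supported.
- A reader might take 18 points as the loss on each key comparison. It is the loss for beating both comparators when these are equal, and the protocol sets no such joint criterion.
- A reader might infer that leaving the method open is itself a defect. The article defers details to an analysis plan that is not shown.
- A reader might join that open choice to the statement that "the statistician will not be blind to treatment allocation" and infer a choice steered by the results. The same section says that checks are in place against bias by the statistician, the Ethics and dissemination section plans no interim efficacy comparison, and nothing suggests that the method would be chosen after seeing results by arm.

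**Conclusion.** The point holds as one of efficiency. In this three-arm design the 5% global test followed by unadjusted 5% contrasts gives strong familywise control of the hypothesis tests, so the anticipated adjustment is not needed for them. Its cost at the planned size and stated effect ranges from about 1 to 3 points per true comparison (Shaffer) to about 5 to 11 points (plain Bonferroni), and reaches about 18 points under Bonferroni for beating both comparators when these are equal.

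The control result needs two conditions: the contrasts come from the same ANCOVA as the global test, and they are tested only after it is significant. The power figures further assume SD 5, no variance reduction from baseline except in the sensitivity check, and third-arm means that the documents do not give. It is not an error in validity, and the trial's conclusions would not be unsound if the adjustment were kept.

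**What to change.** Replace the sentence on adjustment in the Statistical analysis section, and carry the same wording into the analysis plan:

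> If the global ANCOVA F-test is significant at 5%, the three pairwise contrasts from the same model are each tested at 5% two-sided; with three arms this is a closed procedure with strong familywise control, so no further adjustment of the tests is made.

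Add that the pairwise 95% confidence intervals are not adjusted and so have no simultaneous coverage. That is the one small downside. The change needs no extra participants and no new data, gives up no familywise control of the tests, and brings the analysis into line with the Sample size section, which relies on the gate alone.
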